## Abstract

Ninety percent of elderly patients with lumbar disc herniation (LDH) have problems with the mechanics of the spine and muscle tissue. Shi-style spine balance manipulation combined with guidance (Daoyin) of muscle and bone as an alternative therapy for LDH can tone the muscle groups around the spine and maintain optimal mechanical and static sagittal balance of the spine. This study will be performed to investigate the effect of a combination of Shi-style spine balance manipulation and Daoyin therapy on LDH in middle-aged and elderly patients. In this non-blinded, randomized controlled trial, 72 eligible patients will be randomly divided into a treatment group (Shi-style spine balance manipulation combined with Daoyin therapy) and a control group (lumbar mechanical traction). Before and after the intervention, lumbar X-ray and magnetic resonance imaging examinations will be performed to observe the sagittal balance parameters of the spine and pelvis and the lumbar muscle strength. The visual analog scale score, Oswestry disability index score, and pressure pain threshold will be evaluated at baseline and at 2, 4, 12, and 24 weeks. During the treatment period, any signs of acute adverse events, such as paralysis of the lower extremities or cauda equina syndrome, will be recorded at each visit. Although Shi-style spine manipulation combined with Daoyin therapy has been used in the treatment of LDH in middle-aged and elderly people in China for many years, there is no consensus on its effectiveness. This experiment will provide convincing evidence of the efficacy of Shi-style spine manipulation combined with Daoyin therapy in the treatment of LDH in middle-aged and elderly people.

## Introduction

1

The main clinical symptom of LDH is waist and lumbocrural pain. Patients with severe LDH may even develop lower limb paralysis and incontinence.^[1]^ LDH has a high incidence and affects a wide range of people. It has become an important disease that affects peoples health, work ability, and quality of life.^[2]^ The risks associated with surgery are higher in elderly patients because they are more likely to have combined underlying morbidities such as hypertension and diabetes. LDH is characterized by a long disease course, high relapse rate, and difficulty obtaining good outcomes of radical treatment, resulting in long-term suffering. Therefore, the medical field faces a substantial challenge in establishing effective treatment and rehabilitation measures to reduce the incidence of recurrent attacks of LDH.

Research has shown that more than 90% of elderly and middle-aged patients with LDH have mechanical problems associated with their spinal and muscle tissues.^[3]^ Under normal circumstances, the “tendon” system composed of muscle groups and ligaments in the rear of the spine maintains the exogenous stability of the spine (i.e., its dynamic balance).^[4]^ The “bone” system composed of vertebral appendages and intervertebral discs maintains the endogenous stability of the spine (i.e., its static balance). The sagittal balance of the spine and pelvis is an important parameter when evaluating the biomechanical stability of the spine. “Tension band function” from erector spine muscle group of lumbar rear is the key to maintaining orthostatism and sagittal balance of the spine. An imbalance between the dynamic and static forces of the spine,^[5]^ which is associated with sagittal imbalance of the spine and pelvis along with atrophy and fat infiltration of the extensor muscles of the lumbar spine, greatly contributes to the occurrence and development of LDH.

In traditional Chinese medicine, manipulation is the main treatment method for LDH. Using massage to rotate the spine rotation, the protrusion of the nucleus pulposus and position of the nerve roots can be changed to remove adhesions, relieve compression, and expand the nerve root canal. In addition, such manipulation can promote repair of the posterior extensor muscles of the dorsolumbar spine^[6–8]^ by relieving muscle spasm, promoting muscle relaxation, dilating peripheral blood vessels, improving local anemia and anoxia, and eliminating tissue inflammation and edema. Through exercise and Daoyin (guidance) of the lumbar core muscles, the muscle strength of the posterior lumbar multifidus, erector spinae, and psoas major muscles can be enhanced; the coordination and flexibility of the spinal ligaments can be increased; muscle adhesion can be released; muscle elasticity can be restored; and muscle atrophy can be prevented.^[9,10]^ Such therapy plays an important role in maintaining or restoring the optimal balance of mechanical dynamic and static sagittal forces of the spine and pelvis, thus curing and preventing recurrence of LDH. Therefore, establishment of a standardized scheme of manipulation and guidance (Daoyin) in the treatment of LDH is of great clinical significance.

In one retrospective study, the sagittal balance parameters of the spine and pelvis as shown by lumbar vertebral magnetic resonance imaging (MRI) and X-ray examination were compared between 32 patients aged >50 years with LDH at L4/5 and L5/S1 and 32 asymptomatic healthy persons.^[11]^ The study showed that the degree of lumbar lordosis was smaller in patients with LDH (−43.52 ± 14.56 degrees in the LDH group and −48.3 ± 11.1 degrees in the normal group). The pelvic incidence (PI) was also smaller in patients with LDH (45.1 ± 9.6 degrees in the LDH group and 49.12 ± 10.02 degrees in the normal group). The sacral slope (SS) was smaller in patients with LDH (32.05 ± 9.40 degrees in the LDH group and 34.8 ± 7.8 degrees in the normal group), as was the pelvic tilt (PT) (10.3 ± 6.7 degrees in the LDH group and 17.53 ± 8.57 degrees in the normal group). The severity of thoracic kyphosis was greater in patients with LDH (27.6 ± 10.33 degrees in the LDH group and 24.2 ± 9.8 degrees in the normal group). At present, there is a lack of research on the parameters of spinal sagittal balance and lumbar bone structure in elderly patients with complicated LDH treated by spinal balance manipulation combined with Daoyin therapy. The above research results provide an important theoretical basis for the development of our current project, which is also a continuation of previous work. Pelvic traction is beneficial for alleviating the symptoms of nerve root compression and is a common method for treating LDH. There is no clear clinical evidence against the use of traction in the treatment of LDH. Therefore, patients in the control group of our proposed study will be mainly treated with pelvic traction.

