### Sample size calculation

2.9

We estimated the sample size based on the main outcome indicators, and we conducted a randomized trial of Shi-style lumbar spine manipulation combined with Daoyin therapy versus lumbar traction from March to September 2018, with 10 participants in each group. The outcome parameter was the rate of improvement in the NDI (neck disability index) score from baseline to the end of the 8-week treatment. The results showed that the rate of improvement after Shi-based lumbar spine manipulation combined with Daoyin therapy was 92.0%, while that after lumbar traction was 86.6% (*P* = .893) (α = 0.05, test efficiency 1 − β = 0.8, and equivalent standard δ = 0.2).

Because our study protocol will involve the use of a non-inferiority test, according to the number of cases in the clinical non-inferiority and equivalent tests and the equivalent standard,^[17]^ and using counting data (rates) as the outcome indicators, the following formula was used to estimate the number of patients required for this study:$$n=2\times {\left({\text{U}}_{\alpha }+{\text{U}}_{\beta }\right)}^{2}\times \text{p}(1-\text{p})/\delta^{2}$$

2 × (U_α_+ U_β_)^2^was calculated as 12.365, and N was 29.537 after substituting the above figures, and the sample size of each group was about 30 cases; according to the loss rate of 20%, the sample size of each group was 36 cases, and the ratio of treatment group and control group was 1:1, a total of 72 cases.

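### Non-inferiority to traction within 20 percentage points would not by itself support the announced efficacy conclusion, because the protocol gives no traction effect over no treatment or sham

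*Protocol article*

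**What the plan says.** - **Design (Protocol article, Sample size calculation, 2.9).** The sample size is justified with the words "Because our study protocol will involve the use of a non-inferiority test". It uses rates as the outcome and the settings "α = 0.05, test efficiency 1 − β = 0.8" and "equivalent standard δ = 0.2". The inputs are pilot improvement rates of 92.0% (manipulation plus Daoyin) and 86.6% (traction), with 10 participants per group. The constant "was calculated as 12.365, and N was 29.537 after substituting the above figures", which leads to 30 per group, then 36 after a 20% loss allowance, 72 in all.
- **Comparator (Introduction).** Two sentences support traction: "Pelvic traction is beneficial for alleviating the symptoms of nerve root compression and is a common method for treating LDH", and "There is no clear clinical evidence against the use of traction in the treatment of LDH". Neither carries a citation or an effect size.
- **Conclusion announced (Abstract).** "This experiment will provide convincing evidence of the efficacy of Shi-style spine manipulation combined with Daoyin therapy".
- **Analysis (Statistical analyses, 2.13).** This section lists t tests, chi-square or Fisher tests and repeated-measures analysis of variance, with significance at P < .05 and two-sided 90% confidence intervals. It does not compare any interval with the margin.

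**The concern.** A non-inferiority result is relative: it says the new treatment is not worse than the comparator by more than the margin. It becomes a statement about efficacy only when the comparator is known to beat no treatment by more than that margin. On the protocol's own traction rate, a 20-point margin preserves some traction effect only if fewer than 66.6% of these patients would improve without traction (86.6 - 20 = 66.6). The protocol gives no such rate.

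Both arms could improve for reasons common to them, such as natural course or the analgesics that the Intervention section permits. A trial that met the margin could not then separate two treatments that work from two that add nothing. At stake is the interpretation: a result compatible with no specific effect in either arm could be reported as efficacy. This would remain true if the non-inferiority test were written perfectly into the analysis section.

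**Working it through.** **1. Reproduce the stated size.** Inputs from section 2.9: α = 0.05, power 0.8, δ = 0.2, p = (0.920 + 0.866)/2 = 0.893.
- Constant: 2 × (1.645 + 0.842)² = 12.365, so α was used one-sided.
- n = 12.365 × 0.893 × 0.107 / 0.2² = 29.537, about 30 per group; 30 × 1.2 = 36.

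Both printed figures reproduce exactly. The one-sided 5% level also matches the two-sided 90% intervals in 2.13. Non-inferiority is therefore the real basis of the size, not a slip of wording.

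**2. What the margin permits.** Starting from 86.6% under traction, the new treatment could have a true rate as low as 66.6%. The non-improved share would go from 13.4% to 33.4%, a ratio of 33.4/13.4 = 2.5.

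**3. How often two treatments with the same true rate meet the margin.** The rule is assumed, since the protocol states none: the lower limit of the two-sided 90% Wald interval for (treatment minus traction) lies above -0.2. For a shared true rate p and n per arm, the normal approximation is Φ(0.2/√(2p(1-p)/n) - 1.645).
- Example, p = 0.893, n = 30: the standard error is √(2 × 0.893 × 0.107/30) = 0.0798, and Φ(0.2/0.0798 - 1.645) = 0.805.

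Exact binomial enumeration of the same rule gives:

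| Shared true rate | 30 per arm | 36 per arm |
|---|---|---|
| 0.893 | 82% | 88% |
| 0.866 | 76% | 82% |
| 0.80 | 64% | 71% |
| 0.70 | 52% | 59% |
| 0.50 | 45% | 55% |

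The first row is the design power under another name: the trial was sized so that equal arms at 0.893 would pass about 80% of the time. The lower rows are needed because the rate without effective treatment is not given.

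**4. Can the pilot supply the missing traction effect?** No. It compared the two active arms with 10 participants each, so 86.6% is a within-arm figure without an untreated reference.

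**5. Power for superiority on the same rate.** At 92.0% vs 86.6%, two-sided 0.05:
- n = 30: standard error √(0.92 × 0.08/30 + 0.866 × 0.134/30) = 0.0795; 0.054/0.0795 = 0.68; Φ(0.68 - 1.96) = about 10%.
- n = 36: standard error 0.0726; 0.054/0.0726 = 0.74; Φ(0.74 - 1.96) = about 11%, or 12% by the calculation that also counts the opposite tail (11.5%).

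**The case against.** Several points on the other side have force.

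- **The comparator has a positive rationale.** A reader might infer that traction was chosen only because nothing speaks against it. The introduction does not support that: the sentence before says that traction is beneficial and commonly used. This stands. The statement is uncited and unquantified, however, so it cannot show that traction exceeds no treatment by more than 20 points.
- **The pass probability depends on the shared rate.** A reader might infer that two ineffective treatments would pass 80-88% of the time without qualification. That needs both arms to have a true rate near 89%. At lower rates the figure drops to roughly half, as the table shows.
- **No rule ties efficacy to the margin.** A reader might infer that meeting the margin would lead the investigators to declare efficacy. The analysis section lists ordinary difference tests and no comparison with -0.2, and the abstract's sentence is a closing promise, not a decision rule. The step is therefore an inference. What stands is that the sizing section and the abstract point to different conclusions, and nothing in the article bridges them.
- **The margin may be justified elsewhere.** Section 2.9 cites a source for the case numbers and the equivalence standard, and a full protocol may say more. That is fair, so the absence of a margin derivation is not the point made here. The point concerns the conclusion that the article states.

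**Conclusion.** The concern holds in a limited form. Against this comparator, with the information given, non-inferiority within 20 points supports only the statement that the new treatment is not more than 20 points worse than traction. It does not show efficacy. The chance that two treatments without specific effect meet the margin runs from about 45% to 88%, depending on the shared true rate (0.50 to 0.893) and on 30 or 36 per arm. This rests on the assumed 90% interval rule and on reading the pilot figures as proportions, as section 2.9 does. The argument itself does not depend on which row of the table applies. It should be corrected before results are interpreted, because it changes what the trial can conclude.

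**What to change.** In sections 2.9 and 2.13, and in the abstract and discussion:

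1. State that meeting the margin supports only that the treatment is no more than 20 percentage points worse than traction.
2. State that efficacy will be claimed only if superiority over traction is shown (two-sided P < .05) on one prespecified primary endpoint, tested after non-inferiority on that same endpoint. In that fixed order no alpha adjustment is needed.
3. If more than one primary outcome is to carry the claim, control multiplicity. Section 2.7.1 names three primary outcomes (VAS, pressure pain threshold, ODI), and the improvement rate used for sizing is not among them. The endpoint must therefore be named, with a margin on its own scale if it is not the rate.
4. Remove the announced evidence of efficacy as the expected result of a non-inferiority finding.

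**Cost.** Wording and one ordered test on data already planned; no more patients and no change to treatment. The downside is a narrower claim if only non-inferiority is shown. If superiority is tested on the improvement rate, power is only about 10-12% at the pilot rates, so an efficacy claim on that endpoint would be unlikely. That should be weighed when the endpoint is chosen.

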### Trial design

1.1

We herein describe the study protocol for an outcome assessor-blinded and data analyst-blinded prospective randomized controlled clinical trial.

## Method/design

2

The purpose of this prospective randomized controlled clinical trial is to investigate whether Shi-style spine manipulation combined with Daoyin therapy can lead to improvements in middle-aged and elderly patients with LDH. The study will be conducted in the Department of Orthopaedics, Longhua Hospital, Shanghai University of Traditional Chinese Medicine. The principal investigator will be responsible for the entire project, including organization of the steering committee meetings. An independent steering committee will be responsible for participant safety, meetings, participant recruitment, and quality control. The coordination center will be responsible for communicating protocol modifications and providing materials. The trial will involve 4 weeks of treatment and 6 months of follow-up. After randomization, the patients will receive one course of treatment within 4 weeks. The results will be evaluated at baseline and at weeks 2, 4, 12, and 24.

### Eligibility criteria

2.1

#### Inclusion criteria^[12]^

2.1.1

Male or female participants who meet the following criteria will be eligible for the study:

Provision of written informed consentSatisfaction of the diagnostic criteria for LDHAge of 40 to 75 yearsLDH duration of > 3 monthsWillingness to complete the required spinal balance manipulation treatment and Daoyin training on a voluntary basis

#### Exclusion criteria

2.1.2

The exclusion criteria are as follows:

Age of <40 or >75 yearsPast or current participation in other clinical investigations within the last 3 monthsHistory of failed nonsurgical treatment for 6 months with aggravation of symptomsObvious decrease in muscle strength within a short period of time (muscle strength grade < 3) with symptoms of cauda equina syndromeImaging diagnosis of complete intervertebral disc protrusion and prolapseHistory of severe lumbar trauma and lumbar surgeryPregnancy or preparation for pregnancyHistory of opioid analgesics, sedative hypnotics, or alcohol abuseSystemic diseases such as malignant tumors, diabetes, severe rheumatism, or severe osteoporosisFailure to understand or sign informed consent

The individuals performing the participant recruitment, which is currently ongoing, were selected from the staff at Longhua Hospital Affiliated to Shanghai University of Traditional Chinese Medicine and its sub-centers. Prospective participants are being interviewed and informed of the eligibility criteria and procedures by the coordinator. Eligible participants are first be screened by a baseline assessment and then diagnosed based on their clinical presentation, physical examination findings, and imaging results. All patients are informed that participation in the trial is strictly voluntary and that they can withdraw from the trial at any time. If the patients choose to quit, the collected data will not be deleted; instead, it will be used for the final analysis. A compilation table containing all variables of interest and all potential risks will be completed by the research center. The information obtained will be stored in an electronic database for subsequent statistical analysis. Recruitment began in January 2020 and is expected to end in September 2021. The final follow-up of all participants will be completed by December 31, 2021. The participant processing and evaluation schedule is shown in Figure 1.

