##### Lumbar flexion

2.4.2.2

The patient is placed in the supine position with the hips and knees flexed and the front of the thighs touching the abdomen. The physician stands on the right side of the patient, holding the patients legs with his or her left hand and lifting the patients hips with his or her right hand, thus extremely flexing the lumbar spine; this process is repeated 3 to 5 times.

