##### Tilt

2.4.2.3

The patient lies on the right side first, with the right lower limb straight, the left lower limb flexed with hip and knee bent, the right hand straightened, the left hand flexed with the elbows on the waist, and the head lifted back later. The doctor stands on the right side of the patient, presses the patients left shoulder with his left hand and pushes backwards, and presses the right elbow to press the patients left iliac part and twists forward. Then let the patient turn over and repeat the above diagonal wrench method.

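### The neurological exclusion requires rapid weakness and cauda equina symptoms together, so as printed neither sign alone keeps a patient out

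*Protocol article*

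**What the plan says.** Section 2.1.2 lists ten exclusion criteria. The fourth concerns an obvious short-term loss of strength and reads in part "muscle strength grade < 3) with symptoms of cauda equina" syndrome. The item before it excludes "failed nonsurgical treatment for 6 months with aggravation of" symptoms, and a later one excludes a history of "severe lumbar trauma and lumbar" surgery. The same section says that eligible participants are "then diagnosed based on their clinical presentation, physical examination findings, and imaging results".

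Elsewhere, the Introduction says of the disease itself: "Patients with severe LDH may even develop lower limb paralysis and incontinence". Section 2.8 (Safety assessment) gives lower limb paralysis and cauda equina syndrome as examples of acute reactions to ask about after treatment, joined there by *or*. Section 2.14 (Monitoring) has supervisors visit twice a month and audit, among other things, the inclusion and exclusion criteria.

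**The concern.** Rapid severe weakness and cauda equina symptoms are each a warning sign. As printed, the criterion acts only when the two coincide, so the patient with one of them passes.

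Both arms load the lumbar spine. In the treatment arm, one step of the manipulation is described as "thus extremely flexing the lumbar spine" (section 2.4.2.2). In another, the practitioner "presses the right elbow to press the patients left iliac part and twists forward", after which the patient turns over and the movement is repeated (section 2.4.2.3). In the control arm, traction starts at 25% to 30% of body weight and rises by 2 kg a session towards 40% to 60%, as tolerated (section 2.6). Asking about harm after each session, as section 2.8 requires, comes after exposure; the exclusion criterion is the step that prevents it.

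What is at stake is patient safety and consistent application of the rule across the hospital and its sub-centres, not the validity of the estimate.

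**Working it through.** No arithmetic beyond counting applies. The check is a reading of the text.

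**1. What the item does, case by case.** Let W be a rapid fall in strength to below grade 3, and C be symptoms of cauda equina syndrome.

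| Patient has | Excluded by the item as printed (*with*) | Excluded if *or* |
|---|---|---|
| W and C | yes | yes |
| W only | no | yes |
| C only | no | yes |
| neither | no | no |

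The two wordings differ in exactly the two single-sign rows.

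**2. Does another criterion cover those rows?**

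- Inclusion (section 2.1.1), 5 items: consent, diagnostic criteria, age, duration, willingness.
- Exclusion (section 2.1.2), 10 items: age; other studies; failed treatment with aggravation; strength loss with cauda equina symptoms; imaging finding; trauma and surgery; pregnancy; opioid, sedative or alcohol abuse; systemic disease; consent failure.
- Total: 5 + 10 = 15.
- Items that name muscle strength or cauda equina symptoms: 1 (the fourth exclusion).
- Items that exclude on either sign alone as worded: 0. After the change to *or*: 1, which then acts on each sign.

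The imaging item and the failed-treatment item could remove some single-sign patients, but neither is defined by weakness or by cauda equina symptoms, so they do not close the gap.

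**3. Is there a textual reason to read *with* as *or*?**

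- The preceding item uses *with* jointly: failed treatment and worsening symptoms are both needed.
- Six of the ten exclusion items mark alternatives with *or*: age, study participation, pregnancy, substance abuse, systemic disease, consent failure.
- Section 2.8 joins paralysis and cauda equina syndrome by *or*. Paralysis is not the same as strength below grade 3, and that section sets no eligibility rule, so this shows only that the authors regard the two as separate serious events.

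Nothing in the list tells a reader to take *with* in any but its ordinary joint sense.

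**4. Consequence for oversight.** If the section 2.14 audit is done against this wording, a single-sign patient counts as eligible and is not flagged.

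**The case against.** The strongest reply is that nobody meant this. The list is loosely drafted: the trauma and surgery item uses *and* where two separate histories are probably intended. If connectors in the list are not strict operators, a strict reading of one of them says little about the rule applied in practice. That is a fair account of intent, and no decision to admit such patients is alleged. It does not make the printed rule correct.

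A second reply is that such a patient would not get through. Screening covers presentation, examination and imaging, it takes place in an orthopaedic department, two other exclusions overlap in part, traction is limited by tolerance, and "An independent steering committee will be responsible for participant safety". This stands as a reason to think the event unlikely. It means, however, that protection comes from clinicians overriding the wording.

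A third is that the article condenses a full protocol that may read differently, and that the auditors may work from that document. This also stands, and it limits the finding to the printed text. But the item is not something left out for brevity; it is stated, and stated wrongly.

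Finally, the Introduction joins paralysis and incontinence by *and*, so it does not itself show that single-sign patients present. It shows only that such signs belong to the disease, which makes one of them at screening plausible rather than documented.

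**Conclusion.** The concern holds. Followed as written, section 2.1.2 excludes a patient only when rapid severe weakness and cauda equina symptoms are both present, and none of the 15 printed criteria excludes on either sign alone. That count describes the text and is not an estimate of risk: the document does not say how many such patients appear at screening, and the number may be small. Two things are assumed: that *with* carries its ordinary joint meaning, and that the printed list is the one applied. The correction should be made because the possible harm is serious and the remedy trivial, though the likelihood is low. Sample size and statistical analysis do not depend on it.

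The trauma and surgery item is a weaker, secondary point. Read literally it does not exclude previous lumbar surgery alone, but it can also be read naturally as listing two separate excluding histories.

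**What to change.** Replace *with* by *or* in the fourth exclusion criterion, so that it covers a rapid fall in strength to below grade 3, or any symptoms of cauda equina syndrome, each sufficient alone. Splitting it into two items would do the same. In the same amendment, replace *and* by *or* in the trauma and surgery item. If the full protocol already reads this way, only the article needs correcting.

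The cost is one word in each of two criteria. Recruitment is ongoing, so it has to be made by amendment and passed to all recruiting staff. The only downside is possibly a few more screening failures.

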### Data collection and monitoring

2.12

This is a 24-week clinical trial in which the participants will undergo the research intervention for 4 weeks with a 24-week follow-up. The primary outcome measures will be assessed at 5 time points (at baseline and at weeks 2, 4, 12, and 24), the secondary outcome measures will be assessed at 2 time points (at baseline and at week 24), and safety will be assessed at 6 time points (at baseline and at weeks 1, 2, 4, 12, and 24). All results will be independently documented by 2 investigators using EpiData version 3.1 (EpiData Association, Odense, Denmark), and differences will be resolved through discussion with a third investigator. The Longhua Hospital Affiliated to Shanghai University of Traditional Chinese Medicine will be responsible for monitoring and quality control.

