### Statistical analyses

2.13

Trained statisticians will use the intentionality approach for validity assessment and safety analysis. The final outcome observation method will be applied to deal with missing values. All statistical analyses will be performed using SPSS version 22.0 (IBM Corp.). Before randomization, the patients baseline characteristics will be collected as descriptive statistics, including sex, age, body mass index, duration of symptoms, and degree of LDH. The data analysis of the primary outcome will be based on the per-protocol population as a supportive analysis. The mean, standard deviation, median, quartiles, and interquartile ranges will be calculated for continuous variables, and the frequency will be calculated for categorical variables. Continuous variables with a normal distribution will be calculated by the independent-samples Student *t* test and presented as mean with standard deviation; otherwise, the data will be analyzed using non-parametric tests and expressed as median with range.

Categorical variables will be expressed as number (%) and analyzed by the χ^2^ test or Fisher exact test. Repeated-measures analysis of variance will be used to analyze the changes in the VAS score, PPT, and ODI score at different time points (baseline and weeks 1, 2, 4, 12, and 24). An independent-samples *t* test will be used to analyze the changes in lumbar lordosis, lumbar vertebral angle, tilt angle of the first thoracic vertebra line, PI, PT, SS, and LM at baseline and 24 weeks. A *P* value of <.05 will be defined as statistically significant, and two-sided 90% confidence intervals will be calculated. Missing data will be input with the last observed response carried forward for all measures using the “last-value-carried-forward” principle.

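### Recruitment into September 2021 and final follow-up of everyone by 31 December 2021 cannot both hold with a week-24 assessment

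*Protocol article*

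**What the plan says.** The calendar stands in the recruitment paragraph at the end of section 2.1.2 (Exclusion criteria) of the protocol article. Recruitment started in January 2020 and "is expected to end in September 2021. The final follow-up of all participants will be completed by December 31, 2021".

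The visit schedule appears twice. Section 2 (Method/design) states: "The results will be evaluated at baseline and at weeks 2, 4, 12, and 24". Section 2.12 (Data collection and monitoring) repeats it for the primary outcomes: "The primary outcome measures will be assessed at 5 time points (at baseline and at weeks 2, 4, 12, and 24". The same section places the secondary outcomes, which are the sagittal X-ray parameters and MRI lumbar muscularity, at baseline and week 24 only.

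For gaps in the data, section 2.13 (Statistical analyses) has one rule: "Missing data will be input with the last observed response carried forward for all measures".

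Nothing in the article shortens follow-up for late recruits or gives a later closing date.

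**The concern.** The interval from the planned end of recruitment to the planned end of follow-up is three to four months, while the schedule needs 24 weeks per patient. Anyone enrolled late in the window cannot complete the schedule before the stated closing date.

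Two things are at stake if the dates are followed as written.

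- **Imaging outcomes.** Week 24 is the only post-baseline X-ray and MRI. A patient without it has nothing but the baseline image to carry forward, so the analysed change is exactly zero. The effect on sagittal balance and lumbar structure is a declared aim in the Discussion.
- **VAS, PPT and ODI.** The week-12 value would be used for week 24. In the treatment group Daoyin continues for 6 months (section 2.3), so week 12 falls about halfway through that course.

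Missing values of this kind are set by the calendar, known in advance and avoidable.

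**Working it through.** **Inputs.** Recruitment from January 2020 to September 2021 and closing date 31 December 2021 (section 2.1.2); last assessment at week 24 (sections 2 and 2.12); total sample 72 (section 2.9). The article gives no day of the month for the start or end of recruitment, so both ends of each month are used. Weeks are counted from enrolment. The article calculates no closing date, so there is no figure of its own to reproduce.

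**Step 1: last feasible enrolment.** 24 weeks × 7 = 168 days. 31 December 2021 − 168 days = 16 July 2021.

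**Step 2: how far a September recruit gets by 31 December 2021.**

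| Enrolled | Days available | Weeks available | Week 12 falls on | Week 24 falls on |
|---|---|---|---|---|
| 1 Sept 2021 | 121 | 17.3 | 24 Nov 2021 | 16 Feb 2022 |
| 30 Sept 2021 | 92 | 13.1 | 23 Dec 2021 | 17 Mar 2022 |

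Week 12 can be reached in every case. Week 24 cannot be reached in any.

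**Step 3: number of patients affected, if both dates are kept and accrual is even.** Number = 72 × (recruitment days after 16 July 2021) / (all recruitment days).

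| Start | End | Days after 16 July | All days | Share | Patients of 72 |
|---|---|---|---|---|---|
| 1 Jan 2020 | 1 Sept 2021 | 47 | 610 | 7.7% | 5.5 |
| 31 Jan 2020 | 1 Sept 2021 | 47 | 580 | 8.1% | 5.8 |
| 1 Jan 2020 | 30 Sept 2021 | 76 | 639 | 11.9% | 8.6 |
| 31 Jan 2020 | 30 Sept 2021 | 76 | 609 | 12.5% | 9.0 |

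The result is about 5 to 9 patients. It would be higher with faster accrual late in the window, lower with slower accrual, and zero if recruitment closed by 16 July 2021.

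**Step 4: what carry-forward does to the imaging comparison.** Suppose a share f of each group has its change set to zero, the true mean difference in change is D in early and late recruits alike, and nothing else is missing. The expected observed difference is then (1 − f) × D + f × 0 = (1 − f) × D. With f from 0.077 to 0.125, the difference shrinks to between 0.923 D and 0.875 D, a loss of about 8% to 12%. This applies only to parameters that can change. Section 2.7.2.3 describes pelvic incidence as relatively constant, so a zero change alters little there.

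**The case against.** The strongest reply is that the article does not say late recruits will be cut off. It schedules week 24 for everyone and says September is only expected. In practice recruitment could close earlier or the closing date could slip, and then no value would be imputed. This stands, and it limits the consequences: a reader might infer that patients are missing at week 24 by design, but the imputation follows only if both dates are kept. It does not remove the conflict, because the dates and the schedule cannot all be met as written. Figure 1, which is not shown, could not cure a contradiction in the text.

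It can also be said that the primary outcomes are largely intact. This is partly right: even the latest recruit can supply weeks 2, 4 and 12, and the article does not name week 24 as the single primary time point. The loss falls mainly on the imaging outcomes.

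Three stronger readings are tempting, and the document does not support them.

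- **That late recruits use up most of the 20% loss allowance.** Section 2.9 raises 30 to 36 per group, an allowance of 6 per group or 12 in total. Patients whose values are carried forward stay in the analysis and are not lost in that sense. The sample size also rests on an improvement rate at the end of an 8-week treatment, not on week 24.
- **That every secondary outcome is diluted.** Pelvic incidence is the counter-example.
- **That 28 weeks are needed, with more patients affected.** Section 2 says "The trial will involve 4 weeks of treatment and 6 months of follow-up" and section 2.12 says "the participants will undergo the research intervention for 4 weeks with a 24-week follow-up", which could be read as follow-up starting after treatment. But section 2.12 also calls this a 24-week trial, and no assessment is scheduled at week 28.

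**Conclusion.** The plan is wrong as written: enrolment into September 2021, final follow-up of all participants by 31 December 2021 and a week-24 assessment for everyone cannot all be met. That part is calendar arithmetic and depends only on counting weeks from enrolment. The cut-off is 16 July 2021.

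The size is conditional. If both dates are kept and accrual is even, about 5 to 9 of 72 patients (8% to 12%) would lack week 24. Under the further assumptions in step 4, the imaging differences that can change would be attenuated by a similar percentage. The effect on VAS, PPT and ODI is the substitution of week 12 for week 24 in the same patients; its size cannot be worked out from the document.

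**What to change.** Reconcile the dates in section 2.1.2 with the schedule in sections 2 and 2.12, in one of two ways:

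- set the final follow-up date at 24 weeks after the last enrolment, which is 17 March 2022 for an enrolment on 30 September 2021; or
- keep 31 December 2021 and close recruitment by 16 July 2021.

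The first option costs up to 76 days (31 December 2021 to 17 March 2022), about 11 weeks, of extra follow-up for the last patients. The second shortens the recruitment window by 47 to 76 days, with the risk of falling short of 72. Either is a change of one sentence. The article describes recruitment as ongoing, so the correction should be made before late recruits pass the closing date, because a missed week-24 image cannot be recovered.
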